The fundamental questions guiding our entire research project are: What is the effect of TCM therapeutic strategies in the improvement of symptoms resulting from renal replacement therapy in CKG G5 patients undergoing HD? Does acupuncture have a positive effect on FC and health-related quality of life (HRQOL) in hemodialysis patients? If it does, are the results maintained over the long term? In addition, what is the effectiveness of short-term intensive interventions when compared to less frequent and prolonged interventions? Is it possible to integrate acupuncture into the dialysis care routine? Given our research project and the complexity of CKD, the objectives of this study are: (1) to assess the effect of acupuncture on FC and HRQOL in patients undergoing hemodialysis; (2) to evaluate the specific effects of acupuncture as compared to a placebo; (3) to evaluate short- and long-term effects of acupuncture; (4) to determine the difference between short-term intensive and ongoing but less frequent acupuncture treatments; (5) to assess the feasibility of integrating acupuncture in dialysis care.

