## 3. Outcome Measurement

### 3.1. Primary Outcome

The primary outcome measure will be the change in the parameters of FC and HRQOL. FC will be measured by a 6-Minute Walk Test (6MWT) [28]. The 6MWT assesses the submaximal level of functional exercise capacity and is simple and convenient to carry out. Changes in the distance walked in 6 minutes will be used to evaluate the efficacy of therapeutic interventions.

Quality of Life will be assessed by Kidney Disease Quality of Life-Short Form (KDQOL-SFTM 1.3) [29]. The KDQOL-SF contains eight generic subscales that assess various aspects of HRQOL and has been widely used in CKD.

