### 3.4. Statistical Analysis and Sample size

Demographic and clinical data for each group at baseline will be compared using Fishers’ Exact Test (categorical variables) and one-way ANOVA (continuous variables). Two-way repeated-measures ANOVA with interaction between time (baseline, 3 weeks, 9 weeks and follow-up period 12 weeks after treatment) and group will be used to assess the effect of the treatment. Differences over time within each group and subgroup will be assessed with repeated-measures ANOVA, and differences among groups at each moment will be evaluated with one-way ANOVA. A significance level of 5% will be used; differences will be considered statistically significant for *p*-value < 0.05. Statistical analysis will be performed with IBM SPSS Statistics software, version 27.0, IBM, New York, NY, USA [33].

For the sample size, a minimum of 20 patients in each group (experimental, placebo and control groups) was estimated to achieve a small to medium effect size (f = 0.19) [34] in the two-way repeated-measures ANOVA, with a statistical power of 80% and a significance level of 5%. Sample-size calculations were carried out using G*Power V.3.1 [35]. Assuming a possible dropout rate of 15%, a minimum of 24 patients will be randomly selected for each group. In the experimental and placebo groups, half of the patients (*n* = 12) will be placed in subgroup A, with three acupuncture sessions per week over 3 weeks, and half (*n* = 12) will be placed in subgroup B, with one acupuncture session per week over 9 weeks.

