Many pharmacological interventions for people with CKD have known risks of adverse events and, according to the literature, acupuncture is commonly used in symptom management for chronic diseases as well as in palliative care [42]. However, the safety and efficacy of acupuncture for people with CKD remains largely unknown. Considering the aims of our study, we expect that verum acupuncture compared to sham acupuncture and non-acupuncture will improve the functional capacity of hemodialysis patients, as evidenced by an increase in the distance walked on the 6MWT and an increase in scores for quality of life. In addition, we expect an increase in handgrip strength and an improvement in peripheral muscle strength. According to Kim et al. (2016), there was low-quality evidence of the short-term effects of manual acupressure as an adjuvant intervention for fatigue, depression, sleep disturbance and uremic pruritus in patients undergoing regular hemodialysis [19]. Under this assumption, this study protocol was designed to check the effect of acupuncture after treatment and at 12 weeks post-treatment. In this way, we expect that the effect of acupuncture will be maintained in the follow-up period.

Some studies, especially in the pain field, suggest that three treatments per week obtain better results than one treatment per week [43,44]. We also expect to see better results with more intensive interventions compared to less frequent and prolonged interventions.

Following review of the literature and to the best of the authors’ knowledge, there are currently no comparable studies. Therefore, our trial seems to be an innovative study for exploring the effect of acupuncture and the frequency of treatment on improving FC and HRQOL in patients undergoing HD. Furthermore, supported by only a few clinical cases reported (personal data) prior to the design and development of the research project, it is possible to predict efficacy and the advantages of integrating acupuncture treatments into routine hemodialysis as a complementary therapy to conventional treatments.

Despite fulfilling strict methodological criteria, it is possible to identify limitations in our study protocol. First, the sample size; second, the TCM practitioner performing the acupuncture treatment will not be blinded due to the nature of the intervention; third, comorbidities inherent to chronic kidney disease may lead to a high dropout rate during the follow-up period.

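### Section 3.4 implies the group-by-time interaction is the lead test, but applies the same unconditional 5% rule to one-way ANOVAs at each visit and to within-group tests

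*Protocol article*

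**What the plan says.** All the analysis rules are in section 3.4 of the protocol article.

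- **Lead test (implied).** "Two-way repeated-measures ANOVA with interaction between time (baseline, 3 weeks, 9 weeks and follow-up period 12 weeks after treatment) and group will be used" to judge whether treatment works. The sample size refers to the same two-way repeated-measures model: f = 0.19, 80% power, 5% significance, 20 per group, raised to 24 for 15% dropout.
- **Further between-group tests, followed directly by the significance level.** "differences among groups at each moment will be evaluated with one-way ANOVA. A significance level of 5% will be used".
- **Within-group tests.** "Differences over time within each group and subgroup will be assessed with repeated-measures ANOVA".
- **One significance rule for all of them.** "A significance level of 5% will be used; differences will be considered statistically significant for" p-values below 0.05.

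Section 3.1 defines the primary outcome as change in functional capacity and quality of life, and says of the walk test: "Changes in the distance walked in 6 minutes will be used to evaluate the efficacy of therapeutic interventions". It names no visit. The Introduction lists as an objective "3) to evaluate short- and long-term effects of acupuncture", and the Discussion says "this study protocol was designed to check the effect of acupuncture after treatment and at 12 weeks post-treatment".

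**The concern.** The 5% level and the 80% power belong to one test, the interaction. The visit-wise ANOVAs and within-group tests carry the same significance label, with no condition, adjustment or descriptive status attached. Suppose the interaction for walk distance is not significant, but the ANOVA at one visit gives p = 0.04. Under the text as written that result may be called statistically significant, and it matches a stated objective, either short-term or long-term. The within-group tests add further significant results that compare no arms at all.

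This arises within a single score, so choosing one primary score would not remove it. At stake is whether the error rate of the claims the paper could make is the 5% it states.

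**Working it through.** **1. What the stated 5% refers to.** For the within-between interaction, the noncentrality is λ = f²·N·m/(1−ρ), with df1 = (k−1)(m−1) and df2 = (N−k)(m−1). From section 3.4, k = 3 groups, f = 0.19 and N = 60. The document gives no correlation; ρ = 0.5 and sphericity are assumed.

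- m = 3 measurements: λ = 0.0361 × 60 × 3 / 0.5 = 13.0, df 4 and 114, power 0.819. The smallest N reaching 80% is 58, so 20 per group.
- m = 4 measurements: λ = 0.0361 × 60 × 4 / 0.5 = 17.3, df 6 and 171, power 0.885. The smallest N is 50, so 17 per group.
- Dropout: 20/0.85 = 23.5, so 24 per group.

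The published 20 and 24 are reproduced with three measurements. The sizing therefore matches one interaction test at 5%.

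**2. How many between-group tests one score receives.** The Abstract describes three assessments (baseline, after treatment, 12 weeks later), which gives the interaction plus two post-baseline ANOVAs. Section 3.4 lists four times, which gives the interaction plus three. The baseline ANOVA is left out because a baseline difference is not a treatment effect. If the tests were independent, the chance of at least one false positive would be 1 − 0.95³ = 14.3% or 1 − 0.95⁴ = 18.5%. They are correlated, so simulation is needed.

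**3. Null simulation.** There were 40,000 trials per setting, with three arms of 20, normal data, equal correlation between visits (compound symmetry) and no missing data. The simulation error is about 0.2 percentage points. The table shows the chance that the interaction or any post-baseline ANOVA has p < 0.05:

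| Assumed correlation | Three assessments | Four assessments |
|---|---|---|
| 0.3 | 12.6% | 15.9% |
| 0.5 | 12.7% | 15.9% |
| 0.7 | 12.4% | 15.1% |
| 0.8 | 12.4% | 14.0% |
| 0.9 | 11.4% | 12.7% |

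The interaction alone gives 4.8-5.1%. A separate run gave 11.5-13.0% for three assessments (correlation 0.5 to 0.9) and 12.6-16.1% for four (0.3 to 0.9). Using 24 per arm changes little.

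**4. Where the excess comes from.** At correlation 0.5 with four assessments, the interaction is significant in 4.93% of null trials. Some post-baseline ANOVA is significant in 12.62%, and in 1.75% the interaction is significant too. Hence 4.93 + (12.62 − 1.75) = 15.8%. The 10.9% in brackets is what making the visit-wise tests conditional on the interaction would remove. Over the correlations tried, this part is about 7-8% with three assessments and 8-11% with four.

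**5. Direction.** These counts include any omnibus difference among three arms. Requiring verum to have the highest mean at the significant visit, with the interaction not significant, leaves 2.2-2.6% of null trials with three assessments and 2.9-3.8% with four.

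**6. Does the conditional rule give 5%?** Under equal correlation it does (4.7-5.2%). If correlation decays with time (AR(1), 0.5 to 0.9, four assessments), the uncorrected interaction test gives 6.0-7.6%; with Greenhouse-Geisser correction it gives 4.8-5.1%.

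**The case against.** The strongest reply is that the article does identify its efficacy test. The interaction is the analysis given the job of assessing treatment, and the sample size is tied to it. The visit-wise ANOVAs are described only as looking at differences at each moment, and no sentence says one of them establishes efficacy. The Introduction also asks first whether acupuncture has an effect and only then, if so, whether it lasts, which is in substance an ordered question. A fuller protocol or analysis plan may make the order formal.

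Much of this stands. A reader might infer that the plan has no lead test and that every visit is an equal route to claiming efficacy; the text does not support that. A reader might also infer a 12-16% chance of falsely concluding that acupuncture works. That is not supported either: the count covers any three-arm difference in any direction, the range depends on an assumed correlation, and its upper end needs all four assessments.

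What does not stand is the claim that this is only something left to another document. Section 3.4 states a rule, p < 0.05, and applies it without condition to every test it lists. A later document that made the visit-wise tests conditional would change that rule.

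**Conclusion.** The point holds in a limited form. The interaction is the implied lead test and by itself runs at about 5% when correlations between visits are equal. The text nevertheless allows visit-wise between-group results to be called significant whatever the interaction shows. Per score, this raises the chance of at least one false between-group result to about 11-13% with three assessments and about 13-16% with four. An isolated visit-wise finding that also has verum highest is much rarer, about 2-4% of null trials.

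The figures assume 20 per arm, normal complete data, correlations of 0.3 to 0.9 that the document does not give, and that any significant test would be reported as such. They exclude the within-group tests and the multiplicity across the walk test and the quality-of-life subscales. The wording should be corrected, but the design and sample size are not affected.

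**What to change.** In section 3.4:

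1. State that the group-by-time interaction, with Greenhouse-Geisser correction, is the single confirmatory test for each primary score.
2. State that visit-wise ANOVAs are interpreted as significant only if that interaction has p < 0.05.
3. Report visit-wise results that do not meet this condition, and all within-group and within-subgroup changes, as descriptive estimates with 95% confidence intervals and no significance claim.

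If a deciding time point is preferred to the interaction, define it exactly. Section 2.6 has treatment ending at week 3 in subgroup A and week 9 in subgroup B, so after treatment is not one calendar visit. The 12-week follow-up would then be tested only if the deciding test succeeds.

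The cost is a few sentences, with no extra patients, visits or data. The downside is that an isolated difference at one visit can no longer be claimed as a confirmed effect.

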### 3.6. Quality Control and Data Collection

Before the clinical trial begins, the research team will receive specialized training to ensure the quality of the study is maintained. Topics concerning the research process, eligibility criteria, data collection and management and assessment of adverse events will be covered.

Screening for eligibility, demographic and clinical-data collection and physical examinations will be performed by the TECSAM clinical team, acting as an independent assessor. The main researcher, the practitioner who will provide the acupuncture treatments, will not have access to patient data until anonymization, randomization and allocation procedures are complete. Baseline, after-treatment and follow-up outcome variables will be assessed by the TECSAM head nurse, who will not know to which group each subject is assigned. Moreover, the statistician will be unaware of the allocation details during the research period, to ensure that the objectivity and impartiality of the data are guaranteed.

The clinical trial will be stopped in case of serious adverse events. Participants will be withdrawn from the study if they are reluctant to continue or if they ask to be excluded.

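### The per-visit group tests make no use of baseline, the repeated-measures ANOVA drops any patient missing one time level, and the withdrawal wording adds to the incomplete patients

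*Protocol article*

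**What the plan says.** Section 3.4 (Statistical Analysis and Sample size) names two analyses for comparing groups. The treatment effect is assessed by the interaction of group and time in a two-way repeated-measures ANOVA. Time has four levels: baseline, weeks 3 and 9, and twelve weeks after treatment ends. Then "differences among groups at each moment will be evaluated with one-way ANOVA". No covariate is named for either, and the software is SPSS 27. Section 3.1 defines the primary outcome as change in walking distance and in quality of life.

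On attrition, section 3.4 sets "a minimum of 20 patients in each group (experimental, placebo and control groups") and raises this to 24: "Assuming a possible dropout rate of 15" per cent. Section 4 lists as a limitation that "comorbidities inherent to chronic kidney disease may lead to a high dropout rate during the follow-up period". Section 3.6 states: "Participants will be withdrawn from the study if they are reluctant to continue or if they ask to be excluded".

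**The concern.** Three features of the plan combine.

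- **Precision.** The one-way ANOVAs are the named tests that compare groups at a particular visit, so they bear on the short-term and long-term objective in section 1. They compare raw values and set aside a baseline measurement that every patient is due to have.
- **Incomplete patients.** Classical repeated-measures ANOVA needs a value at every time level. A patient who misses only the last visit therefore leaves that analysis altogether, with any earlier results.
- **Withdrawal wording.** Section 3.6 removes people from the study, not only from the needling sessions, on reluctance alone. Reluctance may well differ between verum, sham and waiting list, and the protocol itself links dropout to comorbidity, which plausibly affects walking distance and quality of life.

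At stake are avoidable loss of precision in a small trial and a main comparison made among completers instead of the groups as randomised.

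**Working it through.** **Inputs from section 3.4:** significance level 5%, power 80%, f = 0.19, three groups, 20 per group before and 24 after the dropout allowance. **Assumed, because the document gives no value:** the correlation rho between measurements (0.5, 0.7 and 0.8 shown) and sphericity (epsilon = 1).

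**1. The plan's own figure.** For the within-between interaction in G*Power, lambda = f² × N × m × epsilon / (1 − rho), with df (k − 1)(m − 1)epsilon and (N − k)(m − 1)epsilon. With k = 3, m = 3, rho = 0.5 and N = 60, lambda = 0.0361 × 60 × 3 / 0.5 = 13.0 on 4 and 114 df. Power is 81.9%, and N = 60 (20 per group) is the smallest balanced size that reaches 80%. The stated figure reproduces. With the four time levels that section 3.4 lists, the same inputs need 17 per group, and power at 60 is 88.5%. Dropout: 20 / 0.85 = 23.5, rounded up to 24, also reproduces.

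**2. Variance for a comparison at one visit.** The factor is 1 for raw values, 2(1 − rho) for change from baseline and 1 − rho² with baseline as covariate.

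| rho | raw | change | adjusted | cut vs raw | cut vs change |
|---|---|---|---|---|---|
| 0.5 | 1 | 1.00 | 0.75 | 25% | 25% |
| 0.7 | 1 | 0.60 | 0.51 | 49% | 15% |
| 0.8 | 1 | 0.40 | 0.36 | 64% | 10% |

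The raw column describes the one-way ANOVAs. The change column describes the interaction test in its simplest two-visit form.

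**3. Per-visit power.** Take f = 0.19 as the size of the group difference at one visit. This is an illustration, since the document gives f for the repeated-measures test. With 20 per group, lambda = 0.0361 × 60 = 2.17 on 2 and 57 df, which gives 23%. Dividing lambda by 0.75, 0.51 and 0.36 gives 2.89, 4.25 and 6.02 on 2 and 56 df, and power of 30%, 42% and 56%.

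**4. Patients left in the repeated-measures ANOVA.** If a share p is missed independently at each of v post-baseline visits, with baseline complete, then 24(1 − p)^v patients per group remain. Power is for the interaction at f = 0.19 and rho = 0.5.

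| p | v = 3: complete of 24 | power | v = 2: complete of 24 | power |
|---|---|---|---|---|
| 5% | 20.6 | 90% | 21.7 | 85% |
| 10% | 17.5 | 83% | 19.4 | 81% |
| 15% | 14.7 | 74% | 17.3 | 75% |

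Both v are shown because section 3.4 lists weeks 3 and 9, while the abstract and section 3.6 describe a single after-treatment assessment. If each subgroup were measured only at the end of its own course, no treated patient would have all four levels. Figure 2 is not available here, so this cannot be settled.

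**5. Total loss.** If 15% of patients are lost overall, 24 × 0.85 = 20.4 per group remain, which is above the planned 20.

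**The case against.** The strongest reply is that the stated test of treatment is the interaction, which has baseline among its levels and so contrasts change, as section 3.1 requires. That stands. A reader might infer that the whole analysis ignores baseline, but this is true only of the per-visit ANOVAs. For the interaction the complaint is one of efficiency, and it shrinks as rho rises: 25%, 15% and 10% in step 2.

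The second reply is that dropout has been allowed for. For power this also stands up to about 15% total loss, and 5% missed at each of three visits still leaves more than 20 per group. A reader might take 15% as the least loss expected, or high dropout as a forecast. The text offers the first as a planning allowance and the second as a possibility.

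Third, the document does not call its analysis complete-case, and missing-data rules are commonly left to an analysis plan. The exclusion of incomplete patients nevertheless follows from the named method and software, so a later plan could keep those patients only by replacing the method. Nor is it right that a patient who misses follow-up has the end-of-treatment result discarded everywhere: the one-way ANOVA at that visit would still use it.

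Finally, a patient who asks to leave must be released. That stands, and the point concerns only the part of the sentence on reluctance. The sentence is condensed, and assessments might continue in practice, but as worded it does not say so.

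**Conclusion.** The point holds in limited form. The per-visit tests forgo a variance reduction of 25% to 64% for rho between 0.5 and 0.8. The interaction test forgoes 10% to 25% in its simplest form. The repeated-measures ANOVA loses patients in proportion to missed visits: power stays above 80% at 5% or 10% missed per visit and falls to about 74% to 75% at 15%. These figures rest on an assumed rho, on sphericity and on independent missingness.

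The more serious issue is bias, whose size cannot be calculated from the document. Recruiting 24 per group offsets lost numbers, but it does not correct for who is lost if dropout follows illness or arm. The documents do not support saying that the trial is underpowered as planned or that its main test disregards baseline. The change is worth making because it needs no further patients.

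**What to change.** - **Model.** In section 3.4, replace both between-group ANOVAs with one linear mixed model (SPSS MIXED) on the post-baseline visits, with baseline value as covariate, group, visit and group-by-visit. Include all randomised patients in their assigned group and use all available data.
- **Contrasts.** Name in advance the end-of-treatment contrast and the follow-up contrast. Treatment ends at week 3 in subgroup A and week 9 in subgroup B, so state which control visit is matched to each.
- **Schedule.** Treatment frequency has no meaning in the waiting-list arm. Code it only within verum and sham, for example through a five-level arm factor.
- **Withdrawal.** Reword section 3.6 so that a patient who stops acupuncture sessions remains in outcome assessment unless consent to follow-up is withdrawn. This concerns data collection only and leaves open when sessions stop.

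The mixed model relies on dropout being explained by the observed data, so the rewording of section 3.6 matters as much as the model. The cost is a minor rewrite of the analysis text, one sentence in section 3.6 and a few extra assessments. Eligible patients attend for dialysis three times a week (section 2.3), so most of these assessments should be within reach.
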